A total of 28 ELCC centers expressed their interest in participation, and of these, 12 ELCC centers were selected for inclusion. While our desired sample size (see sample size calculation below) required the recruitment of 10 ELCC centers, we selected 12 ELCC centers to account for potential center withdrawal. Indeed, 2 centers decided not to continue participation prior to baseline data collection, citing staffing challenges. Following site selection, each ELCC appointed an ELCC-PRO-ECO project liaison (“liaisons”) to connect the research team, ELCC staff, and families. ECE’s and staff at participating ELCC centers during the course of the study were recruited to participate in this study between August 2023 and October 2024.

The PRO-ECO 2.0 study included ELCC centers in 10 different communities across the South Cariboo, East Kootenay, Northern, Southern Interior, Greater Vancouver, Thompson Okanagan, and Vancouver Island regions of British Columbia, Canada. Among the 10 participating ELCC centers, 7 are located in rural locations and 3 in urban locations. In addition, 5 participating ELCC centers are operated on reserve by Indigenous-led organizations.

Children attending a participating ELCC center during the course of the study and their family members were recruited to participate in this study between September 2023 and October 2024. Recruitment of children and families occurred through each ELCC center, posting flyers and distributing letters and emails that outlined details of the PRO-ECO project and sought participation. Center staff also initiated face-to-face conversations with families during drop-off and pick-up times. Over the course of the study, participating children left or graduated from their ELCC center, and newly enrolled children were recruited as the study progressed. Parental written consent was received from participating children. All children attending the ELCC programs were exposed to the PRO-ECO program, either as group 1 or group 2, regardless of consent status.

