### Randomization

Individual ELCC centers served as the unit of randomization in the waitlist control cluster randomized trial design. ELCC centers were randomized to either group 1 or group 2 prior to baseline data collection. Five group 1 centers implemented the PRO-ECO program immediately following baseline data collection, whereas 5 group 2 centers, acting as waitlist control sites, implemented the PRO-ECO program following time 2 data collection. Randomization was conducted by Steering Committee members who randomly drew 5 separate slips of paper with ELCC center names to represent group 1. The research trial coordinator was not blinded to the randomization, and ELCC centers were aware of their group during baseline data collection because planning was already underway with group 1 ELCC centers for launching the implementation of the PRO-ECO project. Data on outcome measures were collected at 3 time points: baseline (time 1), 6-month follow-up (time 2), and 12-month follow-up (time 3). Outcome data aimed to assess the short-term and longer-term outcomes within group 1 and the short-term outcomes within group 2. Data collection occurred during the fall and spring seasons to compare similar weather patterns at each data collection time point.

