The TOPO was implemented through a child-based, observational behavior mapping (OBM) protocol. The purpose of OBM is to understand how an environment supports movement and play behavior by mapping, recording, organizing, and analyzing geographically located data (37). Base maps were developed for each center and uploaded onto digital tablets to facilitate geo-located coding of play behavior. Due to the rural locations and varied geographic distances of most participating ELCC centers, the research team did not code play behavior in situ as was done in the PRO-ECO 1.0 study. Further, in situ coding requires significantly more time, and obtaining reliability in coding requires extensive training, making it unfeasible to have ELCC staff code the play behavior directly on-site. As a result, the liaisons at each center were trained to observe and video record children while outside during scheduled outdoor time. Children were recorded according to a systematic protocol where the liaisons at each ELCC center had a list of consented children. They then captured a 2-minute video of the child’s outdoor play and verbally dictated what they noticed about the play during the video observation. We aimed to collect a total of 64 two-minute videos for each ELCC center at each data collection time point (time 1, time 2, and time 3). The observational data were collected at the child level, where individual children were the unit of observation and observations aimed to capture all consenting children. This differs from the PRO-ECO 1.0 study, which collected observational data at the center level to study children’s outdoor play in connection to their ELCC. Following the collection of videos at each time point, research staff split each 2-minute video into 15-second clips (512 video clips at each center for each time point). Trained and reliable coders coded each 15-second clip to assess the TOPO play types and subtypes. The reliability of the OBM method is defined by the degree of interrater reliability and interrater agreement, which was assessed using weighted κ and intraclass correlation coefficients [43,44]. κ Values of ≥0.70 are commonly accepted as adequate for scientific research [43]. A κ value of 0.82 was achieved between coders in relation to the primary outcome variable (TOPO) prior to beginning video coding.

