### Data Analysis

We aimed to collect 512 fifteen-second video clips at each center for each time point, for a total of 5120 video clips per time point (total N=15,360). This power calculation was based on the statistically significant effect size we observed in the PRO-ECO 1.0 study related to the short-term impact of the program on improving play occurrence (time 1 vs time 2 for group 1 and time 2 vs time 3 for group 2) [23]. The key coefficient of interest is the intervention by group interaction term, which corresponds with a *R*^2^ increase of 0.00295 (ie, variance explained by the special effect), equaling to an effect size of 0.00308, when this interaction term is added to the multivariate regression model. We also expect to have 5 control variables (ie, intervention, group, weather conditions, temperature, and child gender) in the multivariate regression models, which altogether correspond with a residual variance of 0.958. This supports a power calculation of over 99% (0.997) to detect the program effect that we observed in the PRO-ECO 1.0 study. The power calculation was conducted using the G*Power software [50].

To analyze the effect of the PRO-ECO program within the PRO-ECO 2.0 study, we intend to evaluate the change in nature play behavior between pre- and postprogram. The proportion of nature play occurrences compared with nonnature play occurrences across ELCC centers at baseline will be summarized by treatment group using frequencies and percentages. This approach mirrors our analysis in the PRO-ECO 1.0 pilot study [22,23], which demonstrated the effectiveness and significance of measuring children’s outdoor play occurrences through a comparison of play and nonplay behaviors pre- and postprogram implementation. However, in contrast to the PRO-ECO 1.0 study, this study focuses on the occurrence of nature play as the primary outcome variable, and not play participation in general.

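### The stated power of 0.997 treats thousands of fifteen-second clips as independent, although the clips are nested in videos, children and 10 randomized centers

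*Protocol article*

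**What the plan says.** The Randomization section is clear about the unit: "Individual ELCC centers served as the unit of randomization". Five centers went to each group.

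Under Primary Outcomes, the target is 64 two-minute videos per center per time point, each following one child. Then "research staff split each 2-minute video into 15-second clips (512 video clips at each center for each time point").

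The Data Analysis section gives the sample as 512 clips per center per time point, "for a total of 5120 video clips per time point (total N=15,360"). The tested term is the intervention-by-group interaction, with an R-squared "increase of 0.00295 (ie, variance explained by the special effect"), "equaling to an effect size of 0.00308". Five control variables are listed (intervention, group, weather, temperature, child gender), "which altogether correspond with a residual variance of 0.958". G*Power then gives the quoted result: "This supports a power calculation of over 99% (0.997) to detect the program effect that we observed in the PRO-ECO 1.0 study".

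The Inclusion Criteria and Recruitment section relies on this calculation for the number of centers: "While our desired sample size (see sample size calculation below) required the recruitment of 10 ELCC centers". Later in Data Analysis, mixed effects models are planned and randomization at cluster level is acknowledged.

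**The concern.** The regression test assumes that every clip is an independent observation. Here 8 consecutive clips show the same child in the same two minutes, several videos show the same child, and all children in a center share one allocation, one yard and one staff. Cutting a video into 8 pieces multiplies the count by 8 without adding 8 independent pieces of information. The program effect is identified by comparing 5 centers with 5.

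Centers enter the calculation only as a multiplier of the clip count (10 × 512 = 5,120 per time point), not as clusters. Five centers with 1,024 clips each would also give 5,120 clips and the same power. The calculation therefore cannot show that 10 centers were needed.

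At stake is how the result is read. A reader who accepts near-certain power would take a non-significant result as evidence against an effect of the assumed size, when the design may give much weaker grounds for that.

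**Working it through.** **Inputs from the article.** R-squared increase 0.00295; residual variance 0.958; 5 control variables plus the interaction, so 6 predictors; 64 videos and 512 clips per center per time point (8 clips per video); 5,120 clips per time point, 10,240 for two time points and 15,360 for three; 5 centers per group; 193 children filmed over the whole study (Results). Alpha is not stated; 0.05 is assumed.

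**Step 1: reproduce the stated figure.** f² = 0.00295 / 0.958 = 0.00308, as stated. For independent clips, power comes from the noncentral F distribution with noncentrality λ = f² × N:

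| Units taken as independent | Tested predictors | Power |
|---|---|---|
| 5,120 clips | 1 | 0.978 |
| about 7,200 clips | 1 | 0.997 |
| 10,240 clips | 1 | 0.9999 |
| 10,240 clips | 5 | 0.9970 |
| 15,360 clips | 1 | >0.9999 |
| 1,920 videos (64 × 10 × 3) | 1 | 0.68 |

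The article does not say which N, alpha or number of tested predictors lies behind 0.997. Every route found needs thousands of independent clips. Taking the video as the unit, and still ignoring child and center, already lowers power to 0.68.

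**Step 2: allow for the nesting.** Take the contrast of change between two time points, 5 against 5 centers: 10,240 clips and 10 − 2 = 8 degrees of freedom. Stable center differences cancel in a change score, so the component that matters at center level is center-by-period. Total variance is scaled to 1.

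- Variance of a center-period mean: V = ρ_cp + ρ_child/19 + ρ_video/64 + (1 − ρ_cp − ρ_child − ρ_video)/512
- Design effect: DE = 512 × V
- Power from noncentral F(1, 8) with λ = 0.00308 × 10,240 / DE

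Assumed, because the article gives no correlations: ρ_video = 0.3, ρ_child = 0.05, and about 19 children per center per time point (193 / 10). The last divides a study-wide total. Children left and were replaced, so the number per time point may be lower, and that would lower power.

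Example at ρ_cp = 0.01: V = 0.01 + 0.05/19 + 0.3/64 + 0.64/512 = 0.01857; DE = 9.51; 10,240 / 9.51 = 1,077 effective clips; λ = 3.32; power 0.36.

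| ρ_cp | DE | Effective clips | Power |
|---|---|---|---|
| 0 | 4.40 | 2,329 | 0.65 |
| 0.005 | 6.95 | 1,473 | 0.47 |
| 0.01 | 9.51 | 1,077 | 0.36 |
| 0.02 | 14.62 | 701 | 0.25 |

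**Step 3: vary the assumptions.** With ρ_video from 0.2 to 0.5, ρ_child from 0 to 0.05 and ρ_cp from 0 to 0.02, power runs from 0.24 (0.5, 0.05, 0.02) to 0.89 (0.2, 0, 0). With all three correlations set to zero, the same 8-df test gives 0.998. The stated power therefore survives only if the correlations are practically nil.

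**The case against.** The strongest reply is that the article plans mixed effects models and recognizes that randomization is at cluster level. That stands for the analysis: nothing in the article shows that the final test will ignore clustering, and a reader should not infer that it will. But a sound analysis does not make the power figure true. It means that the power was computed for a different model from the one planned.

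A second reply is that such detail belongs in a statistical analysis plan. The point here is not an omission. A specific number is stated, and it does not belong to this design.

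A third is that the true power is unknown and could be fairly high. That is fair: the range reaches 0.89, and the shortfall rests on assumed correlations. A reader might infer that the trial is shown to be badly underpowered, but the article does not support so firm a statement. It does give reasons to expect center-by-period variation: the pilot found marked differences between centers that affected implementation, centers had wide discretion over their modifications (Table 2), and implementation overran in some centers (Discussion).

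It is also tempting to say that 0.997 was computed on all 15,360 clips. The arithmetic does not bear that out, since that count gives more than 0.9999. Nor should the 8 degrees of freedom be carried over to all three time points, where group 2 also receives the program and the contrast is a different one.

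**Conclusion.** The point holds. The power of 0.997 is wrong as written because its unit of analysis is the clip. The arithmetic from R-squared to f² is correct. For a two-time-point comparison of 5 with 5 centers, power is about 0.25 to 0.65 under the central assumptions and about 0.24 to 0.89 over the wider set. These ranges depend on assumed video, child and center-by-period correlations, alpha 0.05 and about 19 children per center per time point. No combination in that set reaches 0.997.

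Two limits apply. The effect size describes play versus nonplay in PRO-ECO 1.0, whereas the primary outcome here is nature play, so even a corrected calculation would use a borrowed effect. For the same reason, and because no expected prevalence of nature play is given, the shortfall cannot be turned into percentage points of nature play from the article alone.

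**What to change.** 1. Withdraw the 0.997 figure.
2. Restate power, or the minimum detectable difference, for 5 versus 5 centers with small-sample degrees of freedom, over a stated range of video, child and center-by-period correlations. A center-by-period value may be sought in the PRO-ECO 1.0 data. Those were coded in situ and collected at center level, so video and child correlations must be assumed or estimated from PRO-ECO 2.0 data.
3. State the N, alpha and tested terms used, and say that the effect size is for play versus nonplay in PRO-ECO 1.0.
4. In Inclusion Criteria and Recruitment, remove or qualify the statement that this calculation required 10 centers. The article gives no other basis for the number, so none should be supplied unless the team can document it.

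The cost is a short recalculation and some rewording. Data collection is complete, so the design does not change and no new data are needed. The downside is a less favorable power statement.

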June 2023	Connecting with participating ELCC^a^ centers in Vancouver, BC (in-person)	Connecting with ELCC centers PRO-ECO values confirmation Research agreement initiation Methodology and data considerations
July to September 2023	Steering Committee connecting (web-based)	Research agreements completion Training on data storage and sharing Data collection tools finalized ECE^b^ training program (Learning Outside Together) finalized
October to December 2023	Steering Committee connecting (web-based)	Celebrations: PRO-ECO 2.0 project officially underway! ELCC center environment modifications guidance development Presentation to the university on the unique partnership of the Steering Committee
January to April 2024	Steering Committee connecting (web-based)	Baseline data collection complete Feedback from participating ELCC centers Progress on PRO-ECO program implementation
January to April 2024	Steering Committee connecting (web-based)	Baseline data collection complete Feedback from participating ELCC centers Progress on PRO-ECO program implementation
May to August 2024	Steering Committee connecting (web-based)	Welcoming family partners Time 2 data collection updates Overview of environment modifications at group 1 ELCC centers (photos and stories)
September to December 2024	Steering Committee connecting (web-based)	Time 3 data collection update Overview of environment modifications at group 2 ELCC centers (photos and stories)
January to March 2025	Steering Committee connecting (web-based)	Celebrations: PRO-ECO 2.0 project complete! Celebrating each ELCC center and their success Early results from the PRO-ECO 2.0 study

^a^ELCC: early learning and child care.

^b^ECE: early childhood educator.

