### Data Collection and Measures

#### Primary Outcomes

Led by the values they identified as guiding the study (Figure 1), the Steering Committee sought to emphasize children’s relationship with the land and care for the environment. Thus, study outcomes were prioritized to understand how the PRO-ECO project influenced children’s engagement with the land. As a result, the primary outcome chosen for the PRO-ECO 2.0 study was the occurrence of outdoor nature play behavior at ELCC centers. While the primary study outcome differs from the PRO-ECO 1.0 study, where the occurrence of play versus nonplay was assessed, children’s outdoor play behavior was still coded using the expanded version of the Tool for Observing Play Outdoors (TOPO) [42]. The TOPO is designed to measure 8 play types (physical play, exploratory play, imaginative play, play with rules, bio play, expressive play, restorative play, and digital play) and one nonplay type, along with corresponding subtypes. For this study, we coded nature play behavior through the TOPO bio play behavior type, which includes subtypes for play (observing; discussing; or interacting with plants, wildlife, or natural materials, as well as playing in a way that demonstrates care or stewardship of the environment or appreciation of nature). To further refine observed nature play behavior, children’s environmental interactions (loose parts, fixed parts, natural elements, manufactured elements) were also recorded and coded.

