Baseline demographic and ELCC characteristics will be summarized by group using means and SDs, medians and IQRs for continuous variables, and frequencies and percentages for categorical characteristics. Bivariable relationships between children’s demographic characteristics and outdoor nature play occurrence, both overall and by group, will be explored to identify potential confounding factors at the individual level, considering randomization occurs at the cluster level. Mixed effects models will be used to assess differences in quantitative outcome measures between groups, as well as within-group comparisons of pre- and postprogram implementation measures.

We will analyze child interviews using qualitative content analysis methods to systematically identify patterns and themes that reflect children’s perspectives and experiences on outdoor play and well-being [51]. The method’s adaptability to diverse data types and research contexts, combined with its structured and systematic analytical process, makes it particularly viable for exploring the wide-ranging and expressive nature of children’s responses. For ECE and family listening circles and interviews, we will use thematic analysis, which involves identifying and analyzing key themes within the data [52]. We will follow a reflexive thematic analysis to facilitate insights regarding ECEs’ and families’ perspectives on various interconnected topics, such as the importance of outdoor play, power dynamics, cultural norms on outdoor play, and the acceptability of the PRO-ECO program.

In alignment with the PRO-ECO project values and the partner research agreements, we will work with participating ELCC centers and the Steering Committee to share ongoing results from this study. Steering Committee members and liaisons will be invited to join a working group to work with the Outside Play Lab team on guiding and interpreting the analyses. We will gather ongoing iterative input from the broader Steering Committee and ELCC center teams to help interpret the findings, guide subsequent analyses, and develop recommendations. This form of member checking will seek to ensure all analyses and results align with the desired outputs of our project partners and appropriately convey the findings.

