## Results

This study was developed to cocreate, administer, and evaluate the PRO-ECO program following the implementation of the PRO-ECO pilot study in 2021. Funding to conduct this study was confirmed in March 2022. Ethics approval was received in September 2022. Recruitment of ELCC centers occurred from January 2023 to June 2023, followed by participant recruitment beginning in August 2023. Baseline data were collected between October 2023 and December 2023, and the group 1 ELCC centers received the PRO-ECO program from December 2023 to April 2024. Group 2 ELCC centers received the PRO-ECO between May and September 2024. Data collection was completed in March 2025. A total of 229 children were recruited to participate in the study, with 193 children participating in observational play videos for coding and 162 children participating in one-on-one interviews. Additionally, 91 staff and educators consented to participate in the study, with 59 participating in focus groups and 84 completing the T-TRiPS survey. In follow-up to consenting for their child to participate, 41 family members completed an interview or family survey to add their perspectives to the study. The PRO-ECO 2.0 waitlist control cluster randomized trial flow diagram is provided in Figure 2.

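### The Data Analysis section does not exempt the primary randomized comparison from partner input given after results are seen, so control of type I error is not assured

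*Protocol article*

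**What the plan says.** The last paragraph of Data Analysis in the protocol article makes three linked commitments.

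- On sharing: "we will work with participating ELCC centers and the Steering Committee to share ongoing results from this study".
- On use: members of the Steering Committee and center liaisons may join a working group that helps guide and interpret the analyses. Iterative input is gathered "to help interpret the findings, guide subsequent analyses, and develop recommendations".
- On aim: "This form of member checking will seek to ensure" is followed directly by the object, which is to "ensure all analyses and results align with the desired outputs of our project partners". A second clause adds that findings should be conveyed appropriately.

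The paragraph comes after both the mixed-model text and the qualitative methods. It does not confine itself to either.

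On the quantitative side, Primary Outcomes states that "the primary outcome chosen for the PRO-ECO 2.0 study was the occurrence of outdoor nature play behavior at ELCC centers". The power paragraph of Data Analysis names the intervention by group interaction as the key coefficient and lists five control variables: intervention, group, weather, temperature and child gender. The mixed models are then to assess "differences in quantitative outcome measures between groups, as well as within-group comparisons of pre- and postprogram implementation measures".

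Table 1 lists "Early results from the PRO-ECO 2.0 study" among the Steering Committee actions for January to March 2025. The Results section says "Data collection was completed in March 2025".

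**The concern.** Member checking is a sound tool for qualitative themes and for the interpretation of any finding. A randomized comparison has a different requirement: the test that decides the trial must not depend on what the results show. As written, the paragraph takes all analyses and results as the things to be aligned, after results have been shared, and has no boundary around the confirmatory test.

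The people consulted are not blind to allocation. Steering Committee members drew the groups, and centers knew their group at baseline (Randomization). Centers also deliver the program, and their liaisons film the outcome videos.

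If the deciding contrast, model or covariates were settled or altered after results by group were known, the reported p-value and confidence interval would no longer have their nominal meaning. That would weaken the article's claim to a rigorous experimental design.

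This is a procedure that the article states, not a detail left to an unseen analysis plan. An analysis plan that locked the primary test would sit awkwardly beside this paragraph unless the paragraph made room for it.

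**Working it through.** **Step 1. Does the article already fix the deciding test?** The relevant places, side by side:

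| Element | What fixes it | What loosens it |
|---|---|---|
| Primary outcome | Primary Outcomes: one, the occurrence of nature play | Abstract: two, proportion and diversity |
| Deciding contrast | Data Analysis, power paragraph: the intervention by group interaction | Data Analysis: between-group and within-group comparisons, unranked |
| Covariates | Data Analysis, power paragraph: five control variables | Data Analysis: child demographics explored against nature play, overall and by group, to find confounders |
| Model | Data Analysis: mixed effects models | Power paragraph: multivariate regression |

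The anchors exist but are loose, and nothing in the article says that the open choices are closed before results are shared.

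**Step 2. The plan's own figure.** The effect size follows from the stated inputs: f² = 0.00295 / 0.958 = 0.00308. Power then comes from the noncentral F distribution with λ = f² × N, one tested predictor of six, and alpha 0.05 (assumed):

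- N = 5120 clips: power 0.978
- N = 10,240 clips: power 0.9999
- N = 15,360 clips: power about 1.000

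The stated 0.997 corresponds to N of about 7198, and the article does not say which N was used. The calculation confirms that one coefficient was singled out. It neither supports nor weakens the point made here.

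**Step 3. What could free choice do?** This is an illustration with these inputs:

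- 5 centers against 5, and three time points (Randomization).
- Two-sided 0.05, assumed because no alpha is stated.
- No program effect and no time trend. Each center has a random effect plus independent center-by-time deviations. Tests are center-level t tests on change scores.

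For nature play occurrence alone, the text allows at least four contrasts:

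1. between-group difference in change from time 1 to time 2
2. group 1, time 1 to time 2
3. group 1, time 1 to time 3
4. group 2, time 2 to time 3

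A fifth is the interaction. The article does not define it, so it is taken here as group 1's change from time 1 to time 2 minus group 2's change from time 2 to time 3.

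Simulation under the null (100,000 trials or more, repeated independently):

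- each test alone: about 0.050
- at least one of the four significant: 0.167
- at least one of the five significant: about 0.185

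**Step 4. Cross-check.** For k independent tests the rate is 1 − (1 − 0.05)^k:

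- k = 4: 1 − 0.95⁴ = 0.185
- k = 5: 1 − 0.95⁵ = 0.226

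These contrasts share data (the first contains the second), so they are not independent and 0.226 does not apply here. For equally correlated normal tests the rates are:

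- correlation 0.5: 0.156 (k = 4) and 0.183 (k = 5)
- correlation 0.8: 0.115 (k = 4) and 0.127 (k = 5)

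The simulated 17% to 19% is consistent with moderate dependence. If the primary test is fixed in advance and kept, its rate stays at 0.05.

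**The case against.** The strongest reply is that the article already names the primary outcome, the key coefficient, five control variables and the model class, and that nothing says these may be replaced. Input that guides subsequent analyses can be read as input on analyses that follow the main one. Member checking is a qualitative term, the paragraph comes straight after the qualitative methods, and the sentence ends with conveying findings. Desired outputs may mean products such as infographics and presentations, which Knowledge Mobilization describes partners choosing. A dated specification of contrast and covariates is ordinary analysis-plan content, which an article may leave out.

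Much of this stands. Three stronger readings are tempting, and the documents do not support them:

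- **That the nominal error rate is lost.** It is not lost if the named test is kept.
- **That partners want a positive effect and a neutral result could be steered towards one.** No sentence says what the desired outputs are.
- **That results by group were already seen in early 2025.** Table 1 does not say what the early results were. They could have been recruitment, qualitative or pooled data. Writing the analysis in the future tense is normal for a protocol article.

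The 17% to 19% also rests on an any-of-several decision rule that appears nowhere in the article, so it can only illustrate.

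What the reply does not remove is the wording. Conveying findings is a separate clause; the first clause makes analyses and results the object, says all of them, and exempts nothing. The named anchors are also inconsistent enough, as step 1 of the working shows, that they do not close the gap by themselves.

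**Conclusion.** The point holds in a limited form. Data Analysis states a procedure under which partner input after results are seen may reach the primary randomized comparison, and it sets no boundary. Control of type I error is therefore not assured. Nothing shows that it has been breached.

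The possible size, under the assumptions set out in the working and if the best of four or five contrasts were freely chosen, is about 17% to 19% against a nominal 5%. Choice of model, covariates or the diversity measure is not counted. A common time trend would make the within-group contrasts reject more often.

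The change is worth making because it is cheap and because the inconsistent anchors leave real room for choice.

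**What to change.** In the last paragraph of Data Analysis:

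1. Limit the member-checking and alignment sentence to the qualitative analyses and to interpreting and conveying the quantitative findings, so that it no longer covers quantitative analyses and results.
2. State that the primary outcome, the deciding contrast, the model and the covariates are those fixed before results by group are shared with the working group, the Steering Committee or the centers.
3. State that any quantitative analysis added or changed after that point is reported as exploratory.
4. If any results by group were among the early results of January to March 2025, say so.

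The cost is a few sentences and no new data. The downside is that quantitative analyses suggested by partners after results are seen carry an exploratory label. Partner governance, the partners' role in choosing outcomes beforehand and in interpretation, and data ownership are unaffected.
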